### 2.3. Statistical Analysis

We will compare outcomes before and after RM via paired *t*-tests in the historical group. We will compare the clinical-, RM-, and device-related variables via independent samples *t*-test between the historic and initiating RM groups. Tests for normality will be provided. If data is non-normal, then *t*-tests and means/standard deviations should be avoided, and Mann–Whitney/Wilcoxon and medians/interquartile ranges should be preferred. For the *t*-tests, we will reject the null hypothesis when the two-sided *p*-value is less than 5%. For the analysis of patient baseline data, continuous variables will be presented as means and standard deviations and analysed using *t*-tests or Wilcoxon rank-sum tests. Categorical variables will be presented as frequencies and percentages. For the analysis of satisfaction with the survey, paired *t*-tests (parametric test) or Wilcoxon signed-rank tests (non-parametric test) will be performed. For surveys conducted only after monitoring, ordinal variables will be analysed using the Mann–Whitney U test, and continuous variables will be analysed using chi-square tests. For patients not completing the follow-up, censoring will be based on the last data collected. Cumulative event probabilities will be estimated with adverse health outcomes, such as patient deaths, inpatient admissions, and MACCEs. Hazard ratios and 95% confidence intervals will be generated with Cox proportional hazards models. For subgroup analyses, the interaction term between the prespecified groups, based on the type of underlying heart disease and LVEF, will be evaluated for the primary outcome. Because of the interim analyses, we will adopt the O’Brien–Fleming method for statistical corrections. For all analyses, we will use two statistical software packages: Stata, version 18 (StataCorp LLC, College Station, TX, USA), and R, version 4.05 (R Foundation for Statistical Computing, Vienna, Austria).

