### 2.2. Data Collection

The baseline data include patient demographic details, such as gender, date of birth, cardiac device type, implantation date, and indication for the device implantation. They also include health conditions (such as a history of hypertension or heart failure) and information on prescription drugs at enrolment, obtained from electronic medical records.

We determined that a historical group is necessary to compare and analyse patients’ hospitalisation rates and satisfaction before and after the application of RM. Patients in the historical group were diagnosed with heart diseases a considerable time before enrolment. They will be compared to patients in the initiating group to determine whether the hospitalisation rate improves with the application of RM.

The two patient groups in this study are as follows: (1) the historical group consisting of patients who already have CIEDs (implanted after January 2020) and have attended outpatient device check-ups (225 patients planned); (2) the initiating group consisting of patients who will undergo CIED implantation after providing informed consent for participation in this study (225 patients planned). We want to investigate the convenience of and satisfaction with RM applications for patients who have yet to experience RM and obtain information on major adverse cardiac and cerebrovascular events (MACCEs) that occurred before RM was applied. Considering the patients’ average lifespan, analysing MACCEs only in the historical group will cause limitations in the future. Therefore, we will also determine the MACCEs in the initiating group for comparison. After informed consent was provided, the patients or their caregivers received a CardioMessenger Smart transmitter (CM) paired with their CIED. The CM collects information through wireless technology (including therapeutic interventions, arrhythmic events, thoracic impedance information, lead data, and device-related alerts), encodes the collected biometric data, and transmits it to a medical institution. Daily RM will be initiated the day after device pairing. In the case of long business trips or other types of extended travelling, patients are asked to take the CM with them and keep it connected to a charger at night near their bedside.

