In this study, we may also use the successor model of the CM family. The package provided to participants will consist of the CM and a power supply module. The CM receives information from the paired CIED once daily, typically at night. The transmitter is used for communication with the CIED, and the data received from the device are encrypted and sent to the company website (www.biotronik-homemonitoring.com/, accessed on 6 February 2025) via the data module. Healthcare providers receive an alert from the website when the device detects a change in the patient’s heart rhythm, identifies issues with the device itself, or prompts a reminder for periodic, overall CIED check-ups.

The ReVe study will be the first prospective multicentre study in South Korea in which the following conditions are fulfilled:(1)Collecting data from all visits or admissions during the study period, classified as device-related, patient cardiovascular condition-related, or non-cardiovascular condition-related events. These visits will also be categorised as either physician-driven (RM-based) or patient-driven hospital visits.(2)Analysing MACCEs, such as myocardial infarctions/cerebrovascular accidents, thromboembolic events, exacerbation of heart failure, admissions due to cardiac causes, cardiac-related mortality (as a proportion of overall mortality), and other cardiac events.(3)Collecting and analysing data on RM variables weekly, including thoracic impedance and lead sensing, to elucidate their correlation with disease progression, admission, and mortality.(4)Evaluating the staffing/time requirements for RM using electronic medical records (log-in and log-out times are recorded).(5)Analysing and comparing patient satisfaction questionnaires after RM every 6 months (Table 1) via telephone or during office visits (between the historical and initiating groups). The questionnaire evaluates the efficacy of RM and the perceived quality of care due to RM. It contains nine questions with five answer categories each (strongly agree, agree, neutral, disagree, and strongly disagree).

Questions (1) to (3) contain the primary outcomes, and (4) and (5) include the secondary outcomes. These are summarised in Figure 1.

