Patients with CIEDs, except those on warfarin or those with other relevant medical issues (followed up on other clinic consultation schedules), are scheduled for routine clinical follow-ups every 3–6 months. Patient satisfaction surveys are scheduled every 6 months to assess changes in satisfaction levels over time and explore varying trends across device types (‘Survey on telehealth patient experience’ by [name], 2023 [15], modified Korean version 1.3; Table 1). The study is summarised in Figure 1, and the process of the study is also available in Supplementary Table S1.

The primary endpoint will be any MACCE after RM (cardiovascular-related death and hospital admissions related to pre-existing cardiovascular disease), defining variables that are predictive of MACCE and unexpected hospital visits during RM. The secondary endpoints will be patient satisfaction with the time, cost, and quality of care after adopting RM (determined via questionnaires on a 6-month basis) and the staffing/time requirements during RM (measured using electronic medical records).

All files and data generated during the study are stored in a safety deposit box or as copied files secured with passwords accessible only to the investigators. Because this study includes personal identifiers and sensitive information, the data will not be openly accessible. Anonymised study data will be made available to researchers upon reasonable request after the study results are published.

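### The plan names a primary endpoint but no deciding contrast or method: two contrasts serve the same RM question, t-tests carry an unshared 5% level, and O'Brien–Fleming covers only the interim looks

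*Protocol article*

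**What the plan says.** **Endpoint.** Section 2.2 of the protocol article gives one composite, and the same sentence goes on to an aim of finding predictors: "The primary endpoint will be any MACCE after RM (cardiovascular-related death and hospital admissions related to pre-existing cardiovascular disease), defining variables that are predictive of". Earlier in 2.2 the allocation is looser: "Questions (1) to (3) contain the primary outcomes, and (4) and (5) include the secondary outcomes".

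**Purpose of the comparisons.** Section 2.2 gives two.
- Within the historical group: "a historical group is necessary to compare and analyse patients’ hospitalisation rates and satisfaction before and after the application of RM".
- Between groups, about the historical patients: "They will be compared to patients in the initiating group to determine whether the hospitalisation rate improves with the application of RM". The same section adds that MACCEs in the initiating group will be determined for comparison.

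**Tests.** Section 2.3 lists three kinds of analysis.
- For change within the historical patients: "We will compare outcomes before and after RM via paired *t*-tests in the historical group".
- For time to event, with no contrast named: "Hazard ratios and 95% confidence intervals will be generated with Cox proportional hazards models".
- For the two groups set against each other: "We will compare the clinical-, RM-, and device-related variables via independent samples *t*-test between the historic and initiating RM groups".

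Rank-based alternatives replace the t-tests if the data are non-normal. The rejection rule, two-sided p below 5%, is stated for the t-tests. The O'Brien–Fleming method is adopted because of the interim analyses. Section 2.1 plans two interim analyses and a final one.

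**The concern.** The two contrasts answer different questions. One is a change within patients who already had a device. The other compares patients with an established device against newly implanted patients. They can disagree: admissions might fall after RM starts in the historical group while the two groups do not differ, or the reverse. The plan does not say which result would then prevail, so an RM benefit could be reported from whichever contrast reaches significance.

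The contrasts are also not equally informative. Under section 2.2 every participant receives a transmitter after consent, and section 2.1 describes the groups as differing in the timing of RM. A between-group difference in events after enrolment therefore reflects time since implantation and patient selection, and is not a comparison of RM with no RM.

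The Abstract states safety and efficacy aims, and the Discussion expects the results to inform guidelines, insurance standards and fees. A claim resting on the wrong contrast would have practical consequences.

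**Working it through.** **1. Does the sample size reveal the deciding contrast?** Inputs from section 2.1: 2-year MACCE incidence 10% to 15%, 95% confidence, 5-point margin. The single-proportion precision formula is n = 1.96² × p(1 − p) / 0.05².
- p = 0.10: 138.3, rounded up to 139.
- p = 0.15: 195.9, rounded up to 196.

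Both match the stated 139 to 196 per group. The calculation estimates one rate in one group. It contains no effect size, power or contrast, so it does not identify a primary comparison.

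**2. How correlated are the two contrasts?** Take equal group sizes n and common variance σ². Let ρ be the within-patient correlation between the before and after periods.
- Before/after difference: variance 2σ²(1 − ρ)/n.
- Historical (after) versus initiating: variance 2σ²/n.
- They share the historical after-RM data, so the covariance has size σ²(1 − ρ)/n.
- Correlation size = (1 − ρ) / [2√(1 − ρ)] = √(1 − ρ)/2.

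This gives 0.50 at ρ = 0 and 0.35 at ρ = 0.5. The documents give no ρ, so 0 to 0.5 is an assumed range. Correlations of 0 and 0.8 are added below as outer limits.

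**3. Chance of at least one false positive from the two contrasts**, from the bivariate normal distribution:

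| Correlation size | Each at 0.05 | Each at 0.0451 |
|---|---|---|
| 0 | 9.75% | 8.8% |
| 0.35 | 9.4% | 8.5% |
| 0.50 | 9.1% | 8.2% |
| 0.80 | 7.8% | 7.1% |

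For independent tests the first entry is 1 − 0.95² = 9.75%.

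**4. Check by simulation.** Under the null, with 225 per group, 2-year rates of 10% and 15%, ρ of 0 and 0.5, and 6,000 runs per setting, the paired and independent t-tests together gave 8.4% to 9.6%. Adding a between-group log-rank test (standing in for Cox) gave 8.5% to 9.7%. Adding a before/after one as well gave 8.8% to 9.7%. Nearly all the inflation comes from having two contrasts. A second method on the same contrast adds little.

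**5. What O'Brien–Fleming does.** With three equally spaced looks (spacing assumed), the nominal two-sided levels are about 0.0005, 0.014 and 0.045. This holds the error of one statistic at 5% over repeated looks. It leaves the choice between contrasts at the same look uncorrected, as the right-hand column above shows.

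**6. After a fix.** One named contrast holds the error at 5% over the looks. If two had to remain primary, a split of 0.025 each gives 1 − 0.975² = 4.94% when independent, before the interim adjustment.

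**The case against.** **Ranking and alpha allocation may be left to a full protocol or SAP.** Absence alone would indeed be no finding. But the article itself gives two contrasts the same job, applies one rejection rule to the t-tests, and confines the correction to the interim looks. That is stated text, and it inflates error as written.

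**A reader might infer that every analysis, Cox included, is tested at a full 5%.** The text does not say so. The 5% rule is stated for the t-tests, the Cox models are described through hazard ratios with 95% confidence intervals, and O'Brien–Fleming puts the final level below 5%.

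**A reader might count deaths, admissions and MACCE under each contrast as separate primary tests** and arrive at a much larger error. The documents give no basis for that. Section 2.2 defines one composite, and no before/after test of death is described.

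**The between-group t-test is worded for clinical, RM and device variables**, not explicitly for the primary endpoint. This stands. That hospitalisation is included follows from reading 2.3 together with 2.2.

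**The between-group contrast might use the historical patients' pre-RM period**, which would supply a period without RM. The text does not say so. It would then set patients who survived to enrolment against newly implanted ones. The correlation in step 2 would have the same size.

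**This is an observational cohort sized for precision, with no trial-level success rule.** This stands and lowers the severity. It does not remove the issue, because the article commits to hypothesis tests and to an interim correction.

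**Conclusion.** The point holds in this limited form. The endpoint is named, but the deciding contrast and method are not. Two contrasts serve the same RM question without sharing alpha, and O'Brien–Fleming does not address that. The chance of at least one false RM claim is about 8–10% with each contrast at 5%, and about 7–9% at a final level near 0.045. These figures assume that either contrast could be used for the claim and that the between-group t-test covers hospitalisation. They also rest on the correlation range shown and, for the lower range, on three equally spaced looks. The Cox models add ambiguity, because their contrast is unstated, but little further error.

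Separately from the error rate, the historical-versus-initiating contrast cannot isolate RM, since both groups receive it after enrolment. Severity is moderate.

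**What to change.** - In section 2.3, name one primary contrast and one method for the composite defined in 2.2, tested at the O'Brien–Fleming-adjusted level. Keep to that endpoint; do not replace it silently with admissions alone.
- If before/after in the historical group is chosen, state that it can cover only the admission component, because everyone enrolled survived the before period. Report cardiovascular death descriptively or by time-to-event analysis. Align the endpoint sentence and the purpose statements in 2.2 with this.
- Label the historical-versus-initiating contrast and the remaining Cox models as secondary, name the contrast each Cox model estimates, and report them with confidence intervals and no claim of RM efficacy. Alternatively, test a second contrast only if the first succeeds (fixed sequence).
- State that the 5% t-test rule is subject to the O'Brien–Fleming levels for the primary test.

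Cost: wording in 2.2 and 2.3, with no new patients or data. Section 2.1 places final data collection in December 2027, so the change can be made before the final data are in, and ideally before any interim comparison. The downside is that only the named contrast, or an ordered second one, can be claimed as confirmatory.

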## 2. Materials and Methods

### 2.1. Study Design

The RemoteVerify (ReVe) study is a multicentre, prospective, observational study that will be conducted at eight university hospitals (St. Vincent’s Hospital, The Catholic University of Korea; Eunpyeong St. Mary’s Hospital, The Catholic University of Korea; Seoul St. Mary’s Hospital, The Catholic University of Korea; Keimyung University Hospital; Kyungpook National University Hospital; Pusan National University Hospital; Yeungnam University Medical Center; Pusan National University Yangsan Hospital) in Korea, targeting 450 patients (each centre will enrol 50 to 70 patients). This sample size was based on the assumption that the 2-year incidence of major adverse cardiac and cerebrovascular events of patients with structural heart diseases is 10% to 15%, with a confidence interval of 95% and a margin of error of 5%. The desired sample size was calculated as 139 to 196 participants per group using G*Power version 3.1.9.7 [16], and similar patients are needed in the two groups that differ in the timing of RM application. Considering an anticipated 10% loss to follow-up during the study period, the total number of participants needed for this study was determined as 442. We rounded this number up to 225 per group. An interim analysis will be conducted using the variables collected by the planned patient enrolment period (24 months). A second interim analysis will be conducted after at least 12 months of follow-up data have been collected. The final analysis will be performed at the study endpoint after all participants have completed the 24-month follow-up. Starting from the interim analysis, subgroup analyses will be conducted based on the type of underlying heart disease (hypertrophic cardiomyopathy/ischaemic cardiomyopathy/dilated cardiomyopathy/others) and the left ventricular ejection fraction (LVEF; <30%, 30–45%, >45%).

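### The non-normality rule in section 2.3 sends per-patient admission and MACCE counts to medians and rank tests, which neither summarise nor target the hospitalisation rate that section 2.2 sets out to compare

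*Protocol article*

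**What the plan says.** Section 2.2 gives the reason for a historical group: to "compare and analyse patients’ hospitalisation rates and satisfaction before and after the application of RM". It adds that these patients will be set against the initiating group "to determine whether the hospitalisation rate improves with the application of RM". Both comparisons are framed as rates.

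Section 2.3 assigns the tests. For the historical group: "We will compare outcomes before and after RM via paired *t*-tests in the historical group". For the two groups: "We will compare the clinical-, RM-, and device-related variables via independent samples *t*-test between the historic and initiating RM groups". If the data are not normal, t-tests and "means/standard deviations should be avoided, and Mann–Whitney/Wilcoxon and medians/interquartile ranges should be preferred". Admission, visit and MACCE counts are not exempted, and no count or rate model is named. The test level is fixed: "we will reject the null hypothesis when the two-sided *p*-value is less than 5" per cent.

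Section 2.3 also plans cumulative event probabilities for deaths, inpatient admissions and MACCEs, and Cox hazard ratios with 95% confidence intervals. The normality rule does not touch these.

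Section 2.1 supplies the event frequency, assuming that "the 2-year incidence of major adverse cardiac and cerebrovascular events of patients with structural heart diseases is 10% to 15" per cent.

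**The concern.** Per-patient counts of a fairly rare event are mostly zeros, so they cannot look normal and the switch to medians and ranks is practically certain. A median says nothing when most patients have no event. Between groups, the null hypothesis of Mann–Whitney is that the two distributions are equal, not that the mean rates are equal. When most values tie at zero, the ranks mainly separate patients with any admission from patients with none, and carry little about how often a patient is readmitted.

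At stake is the hospitalisation comparison for which the historical group was created. Fewer repeat admissions is a plausible effect of earlier detection, and it is the part of a rate that this test hardly sees. Section 2.2 plans to collect all visits and admissions, so the repeat-event data will exist but be little used.

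**Working it through.** **Inputs from the protocol article.** Two-year MACCE incidence 10% to 15% and 225 patients per group (section 2.1); two-sided 5% (section 2.3); implantation after January 2020 and enrolment until October 2025 for the historical group (sections 2.2 and 2.1).

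**Assumptions, not in the document.** The number of admissions per admitted patient. In the simulations a patient is admitted at all with probability p, and an admitted patient has 1 + Poisson(m − 1) admissions, so the mean per patient is p × m.

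**1. What the incidence means.** The plan sizes the study "with a confidence interval of 95% and a margin of error of 5" per cent. The precision formula n = 1.96² × p(1 − p) / 0.05² gives 3.8416 × 0.09 / 0.0025 = 138.3, so 139, at p = 0.10. At p = 0.15 it gives 3.8416 × 0.1275 / 0.0025 = 195.9, so 196. These are the plan's 139 to 196 per group. The incidence is therefore the share of patients with an event, and 85% to 90% have none.

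**2. Is the rule triggered?** Yes. Shapiro–Wilk on simulated counts at n = 225 gives p-values below 10⁻²⁰ at both 10% and 15%.

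**3. The resulting summary.** The upper quartile is 0 whenever fewer than 25% of patients have an event, so at 10% to 15% the summary is 0 (0–0). For other window lengths, assume a constant hazard λ = −ln(1 − p)/2 per year. The share with an event reaches 25% at t = −ln(0.75)/λ:
- p = 0.15: λ = 0.0813, t = 0.2877/0.0813 ≈ 3.5 years.
- p = 0.10: λ = 0.0527, t = 0.2877/0.0527 ≈ 5.5 years.

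The longest possible pre-RM window, January 2020 to October 2025, is about 5.75 years. Long pre-RM windows can therefore give a non-zero upper quartile, and so can all-cause admissions.

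**4. Two fixed examples, 225 per group.**
- 30 admissions in each group, as 10 patients × 3 against 30 patients × 1: t-test p = 1.0, Mann–Whitney p = 0.002.
- 81 against 27 admissions, with 27 patients admitted in each group: t-test p = 0.0005, Mann–Whitney p = 0.64.

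**5. Simulated rejection rates between groups, 225 per group, two-sided 5%.**

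| Scenario (p × m) | Mean per patient | Mann–Whitney | Welch t |
|---|---|---|---|
| 15% × 1.5 vs 10% × 2.25 | 0.225 vs 0.225 | about 30% | about 5% |
| 15% × 2.5 vs 15% × 1.2 | 0.375 vs 0.180 (52% lower) | about 7% | about 78% |
| 15% × 1.5 vs 7.5% × 1.5 | 0.225 vs 0.1125 (50% lower) | about 71% | about 62% |
| 15% × 1.5 in both | 0.225 vs 0.225 | 5% | 5% |

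The first two rows show the mismatch. The last two show that it depends on clustering: Mann–Whitney does well when the share admitted changes, and holds its level when nothing differs.

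**6. Before/after in the historical group.** In a comparable paired simulation, signed-rank power was 75% against 78% for the paired t-test. Larger losses appeared only in constructed cases where a few patients account for most of the earlier admissions. For a fall of about 50% of that kind, with 203 patients (225 less 10%), signed-rank power was 9% to 10% against 37% to 50% for a rate ratio.

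**7. The proposed replacement.** With 203 per group, a rate ratio with person-time offset and robust variance rejected in 4.5% to 5.7% of trials under equal rates. For a 67% fall with the same share admitted, its power was 92% (10% incidence) and 98% (15%), against 5.5% and 8.5% for Mann–Whitney.

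**The case against.** Four objections have weight.

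**The time-to-event analyses.** Section 2.3 plans cumulative probabilities of inpatient admission and Cox hazard ratios, which the normality rule leaves alone. A reader might infer that the study would have nothing to report on admissions except 0 (0–0) against 0 (0–0). The document does not support that: an interpretable time-to-event result will exist. What remains is that, as described, it is not a rate counting repeat admissions, and it is not named for the before/after comparison.

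**The meaning of rate.** Section 2.2 does not define the hospitalisation rate, the primary endpoint is any MACCE, and the sample size uses a proportion. If the share of patients admitted is meant, the rejections in the first scenario reflect a real difference: a chi-square test on any admission rejects in 37% of the same trials. This stands as far as it goes. But on that reading the right summary is a proportion with its interval, and the rule still prescribes a median.

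**Dependence on assumed clustering.** The document gives no figure for admissions per admitted patient, and Mann–Whitney beats Welch when the share admitted halves. The errors are therefore possible, not inevitable.

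**A matter for the analysis plan.** Model detail often belongs there, and this is a condensed article. The point, however, is a rule that the article states and that an analysis plan following it would inherit.

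**Conclusion.** The concern holds in a limited form. Applied as written, the rule gives cardiovascular admission and MACCE counts an uninformative summary wherever fewer than 25% of patients have an event, and a between-group test that does not target the mean rate. The first part follows from the plan's own 10% to 15%. The sizes for the second (about 30% rejection at equal mean rates; about 7% against 78% power) rest on assumed differences in repeat admissions.

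A reader might go further and conclude that the before/after test is equally compromised, or that the summary will be 0 (0–0) for every admission outcome and period. Neither is supported. The paired test loses little power unless a few patients dominate, and all-cause admissions or pre-RM windows beyond about 3.5 years (at 15% incidence and constant hazard) can push the upper quartile above zero. The change should be made before the analyses, but the planned time-to-event results do not depend on it.

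**What to change.** In section 2.3, exempt counts of admissions, visits and MACCEs from the normality, rank and median rule. Compare rates by negative binomial regression, or by Poisson regression, with a log person-time offset and robust variance, clustered by patient for the before/after comparison in the historical group. The offset is needed because pre-RM windows differ between patients while follow-up under RM is 24 months.

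For each group and period, report events, person-time and mean rates, and give the rate ratio with its 95% confidence interval alongside the planned Cox analysis. State in section 2.2 that the hospitalisation rate counts repeat admissions, if that is the intention. Keep rank tests for the ordinal survey items.

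The cost is a change of wording and standard code in Stata or R, the packages already named. No new data are needed. The downside is slightly more modelling than a rank test.

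### Section 2.3 assigns chi-square tests to continuous post-monitoring survey variables, against its own rule for continuous data; probably a slip, and it would cost power on a secondary endpoint

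*Protocol article*

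**What the plan says.** Protocol article, section 2.3 (Statistical Analysis), has one sentence on surveys given only after monitoring has started. It assigns two tests: "ordinal variables will be analysed using the Mann–Whitney U test", and "continuous variables will be analysed using chi-square tests".

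Elsewhere the section treats continuous data differently. For baseline data, "continuous variables will be presented as means and standard deviations and analysed using *t*-tests or Wilcoxon rank-sum tests". Where data are not normal, "Mann–Whitney/Wilcoxon and medians/interquartile ranges should be preferred". Changes in satisfaction are to be tested by paired t-tests or Wilcoxon signed-rank tests. Chi-square is named nowhere else in the article.

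Section 2.2 (Data Collection) describes the questionnaire: "It contains nine questions with five answer categories each", running from strong agreement to strong disagreement, with answers compared "between the historical and initiating groups". It also gives the survey its role: "The secondary endpoints will be patient satisfaction with the time, cost, and quality of care after adopting RM". Table 1 lists the nine items. None is continuous, and no summed or averaged score is defined.

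**The concern.** A Pearson chi-square test needs a table of counts. A continuous variable has no cells until someone groups it, and the article gives no grouping. Once grouped, the test treats the bands as unordered labels: it uses neither their order nor the distance between them, and it gives no estimate of how far apart the groups are.

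All nine items in Table 1 ask about remote monitoring or the transmitter, so they make sense only after monitoring has started. The sentence therefore plausibly governs the comparison of satisfaction between the historical and initiating groups. If the analysts formed a total score and treated it as continuous, the text would send it to chi-square. At stake are lost power, a result that depends on cut-points nobody has fixed in advance, and no effect estimate for that comparison.

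**Working it through.** **1. Consistency within section 2.3**

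| Data | Test named |
|---|---|
| Continuous, baseline | t-test or Wilcoxon rank-sum |
| Continuous, non-normal | Mann–Whitney/Wilcoxon |
| Ordinal, post-monitoring survey | Mann–Whitney U |
| Continuous, post-monitoring survey | chi-square |

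Only the last row departs from the section's rule.

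**2. Group size**

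The article gives no power figure for the survey. Its only sizing figure (section 2.1) reproduces from n = z²p(1−p)/d², with z = 1.96 and d = 0.05:
- p = 0.10: 3.8416 × 0.09 / 0.0025 = 138.3, so 139.
- p = 0.15: 3.8416 × 0.1275 / 0.0025 = 195.9, so 196.

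Both match the stated 139 to 196 per group. The planned 225 per group, less the anticipated 10% loss, leaves 225 × 0.9 = 202.5; 202 is used below.

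**3. Limiting case: every raw value distinct, ungrouped, equal groups**

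Each row holds one patient, with expected counts 0.5 and 0.5, and contributes (1 − 0.5)²/0.5 + (0 − 0.5)²/0.5 = 1. The statistic is therefore N on N − 1 degrees of freedom, whatever the data. At 202 per group that is 404 on 403 df, p = 0.477. At 225 per group it is 450 on 449 df, p = 0.478. The p-value cannot respond to any difference.

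**4. Can the questionnaire produce that case?**

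No. With items scored 1 to 5 (an assumption), nine items sum to between 9 and 45, which is at most 45 − 9 + 1 = 37 distinct values among about 404 patients. Ties are certain.

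**5. Power with ties or grouping**

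Assumptions, none from the article:
- normal data with a shift in SD units;
- 202 per group;
- two-sided 5% level (the article states it for t-tests);
- bands cut at pooled quantiles;
- the integer score is 30 + 6 × the normal value, rounded and held within 9 to 45.

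There were 1,000 simulated trials per shift.

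| Analysis | 0.2 SD | 0.3 SD | 0.5 SD | 0.8 SD |
|---|---|---|---|---|
| t-test | 54% | 85% | 100% | 100% |
| Mann–Whitney | 53% | 82% | 100% | 100% |
| Chi-square, median split | 42% | 70% | 98% | 100% |
| Chi-square, 4 bands | 34% | 63% | 98% | 100% |
| Chi-square, 5 bands | 32% | 61% | 98% | 100% |
| Chi-square, integer score 9–45 | 11% | 22% | 75% | about 100% |
| Chi-square, all values distinct | 0% | 0% | 0% | 0% |

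Analytic check of the t-test at 0.3 SD: 0.3 × √(202/2) = 3.015, and Φ(3.015 − 1.96) = 85.4%. The simulation error is small: at 61%, √(0.61 × 0.39/1000) = 1.5 percentage points.

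The t-test was run on the unrounded values. Rounding adds a variance of about 1/12 to 36, or 0.2%, so it does not explain the gap to the integer score. Much of that gap reflects degrees of freedom: up to 36 for the score, against 4 for five bands and 1 for a median split.

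**The case against.** The strongest reply is that this is a slip of one word. Chi-square is the usual test for categorical data, the section handles continuous data properly elsewhere, and Table 1 contains no continuous item. The ordinal items that do exist are already given Mann–Whitney U. On that view the clause governs no variable the article names, and a competent analyst would not follow it. Most of this stands, and it limits the severity. It does not remove the point: the sentence states a wrong rule rather than leaving detail to an analysis plan, and it would apply to any survey variable treated as continuous.

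A reader might infer more: that the survey comparison has no power, and that p would be near 0.48 whatever the truth. That holds only for distinct, ungrouped values, which this questionnaire cannot produce. With ties or grouping, chi-square reaches 75% to 98% power at 0.5 SD.

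A reader might also extend the point to the staffing and time endpoint. The article does not support that. Section 2.2 takes those times from log-in and log-out records, not from the survey.

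Nor does "Categorical variables will be presented as frequencies and percentages" show that categorical survey data lack a test. That sentence follows directly on the baseline analysis and reads as part of it.

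**Conclusion.** The point holds in a limited form. Section 2.3 names a test for categorical counts for continuous survey variables and so contradicts its own rule; the likeliest explanation is *continuous* written for *categorical*. Followed as written at an assumed 0.3 SD shift, power would fall from about 85% to between 61% and 70% with two to five bands, or to about 22% on an ungrouped integer score. At 0.5 SD the loss is slight with bands (98%) but still material on the integer score (75%, against about 100%).

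These figures rest on the assumed effect sizes, normality, 202 per group and a summed score that the article does not define. They show the scale of the loss and do not predict this study's result. The primary endpoint is untouched. Severity is minor to moderate.

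**What to change.** Rewrite the one sentence so that, for surveys given only after monitoring begins:
- categorical variables are compared by chi-square, or by Fisher's exact test if expected counts are small;
- ordinal items are compared by Mann–Whitney U, as already planned;
- any continuous score is compared by t-test or Wilcoxon rank-sum test, under the section's existing normality rule, with an estimated mean or median difference and 95% CI.

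If a summed score is intended, its scoring should be defined in the same place. Table 1 mixes favourable and unfavourable statements (items 1, 3 and 4 describe discomfort, difficulty and inconvenience), so those items would need to be reversed before summing.

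The cost is one sentence of text. Sample size and data collection do not change, and the correction can be made well ahead of the final data collection planned for December 2027.
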